### 3.0 PROTOCOL SUMMARY

|                                  |                                                                                                                                                                                                                                                                                                                                                                                                                                                                                                              |
|----------------------------------|--------------------------------------------------------------------------------------------------------------------------------------------------------------------------------------------------------------------------------------------------------------------------------------------------------------------------------------------------------------------------------------------------------------------------------------------------------------------------------------------------------------|
| Title:                    | A Phase III, open label, multicenter, parallel group, randomized Clinical Study to compare the Immunogenicity and Safety of Euvichol-Plus vaccine with Oral Cholera Vaccine Shanchol in healthy adults and children above age of one year.                                                                                                                                                                                                                                                                   |
| Phase of Development:     | A Pivotal Phase III Immunogenicity and Safety study for population bridging                                                                                                                                                                                                                                                                                                                                                                                                                                  |
| Indication                | Prevention of Cholera caused by Vibrio cholerae                                                                                                                                                                                                                                                                                                                                                                                                                                                       |
| Background:               | 
Cholera is a significant public health problem in many developing countries. The WHO recommends immunization with cholera vaccines as the complementary management strategy.
 
This study is related to a bivalent (O1 and O139) inactivated whole cell Oral Cholera Vaccine (OCV) containing killed whole cells of Vibrio cholerae O1 and Vibrio cholerae O139. A two-dose regimen of this vaccine was shown to be well-tolerated and immunogenic against Vibrio cholerae.
 |
| Study Centers:            | 8 Centers                                                                                                                                                                                                                                                                                                                                                                                                                                                                                                    |
| Objectives:               | 
Primary:
 
To evaluate the immunogenicity of Euvichol-Plus in healthy adults and children as compared to comparator Oral Cholera Vaccine Shanchol
 
Secondary:
 
To evaluate and compare the safety of Euvichol-Plus with Shanchol in healthy adult and children.
                                                                                                                                                                                                        |
| Investigational Products: | 
Test(A): Euvichol-Plus
 
Comparator(B): Shanchol
 
Two doses of vaccine (1.5 ml per dose) either Euvichol-Plus or Shanchol will be given to subject as per randomization at an interval of two weeks, administered orally.
                                                                                                                                                                                                                                                                  |
| Study Design              | Open label, multi-centric, randomized, parallel group and comparative study.                                                                                                                                                                                                                                                                                                                                                                                                                                 |
| Study Population          | 
416 healthy subjects in step wise two cohorts will be enrolled for the study:
 
 
✓ Cohort 1 subjects <math>\geq 18</math> years to 60 years old
 
✓ Cohort 2 subjects <math>\geq 01</math> to <math><18</math> years old
 
                                                                                                                                                                                                                     |

|                                  |                                                                                                                                                                                                                                                                                                                                                                                                                                                                                                                                                                                                                                                                                                                                                                                                                                                                                                                                                                                                                                                                                                                                                                                                                                                                                                                                                                                           |
|----------------------------------|-------------------------------------------------------------------------------------------------------------------------------------------------------------------------------------------------------------------------------------------------------------------------------------------------------------------------------------------------------------------------------------------------------------------------------------------------------------------------------------------------------------------------------------------------------------------------------------------------------------------------------------------------------------------------------------------------------------------------------------------------------------------------------------------------------------------------------------------------------------------------------------------------------------------------------------------------------------------------------------------------------------------------------------------------------------------------------------------------------------------------------------------------------------------------------------------------------------------------------------------------------------------------------------------------------------------------------------------------------------------------------------------|
|                                  | DSMB will review the 14 days post vaccination safety data of the subjects of cohort 1 and accordingly give its recommendations for the enrolment of cohort 2.                                                                                                                                                                                                                                                                                                                                                                                                                                                                                                                                                                                                                                                                                                                                                                                                                                                                                                                                                                                                                                                                                                                                                                                                                             |
| Sample Size Justification | 
Total Sample size with 10% Dropout is 416.
 
As per published clinical study evaluating immunogenicity of Shancol and Euvichol, the seroconversion rates (4-fold rise in antibody titres) 14 days after first and second dose of vaccine ranges from 73% to 90% in adults and children.
 
Assuming seroconversion rate of 70% in the reference arm, power of 90%, alpha of 5% (2-sided) and a non-inferiority margin of 10%, 186 subjects would be required in the test and reference arms to establish non-inferiority of the vaccine.
 
Considering a dropout rate of 10%, a total of 416 subjects will be enrolled in the study (208 in Test and 208 in reference arms).
 
Approximately 208 subjects enrolled in the study will be adults (<math>\geq 18</math> to 60 years of age) while remaining 208 would be children (<math>\geq 1</math> to <math><18</math> years of age).
                                                                                                                                                                                                                                                                                                                                                                                                                                                                       |
| Treatment Duration        | 28 days                                                                                                                                                                                                                                                                                                                                                                                                                                                                                                                                                                                                                                                                                                                                                                                                                                                                                                                                                                                                                                                                                                                                                                                                                                                                                                                                                                                   |
| Study Methodology         | 
Number of doses and intervals: two doses/Day 0 and Day 14
 
 
- Method of administration: oral administration
 
- Dose of vaccine to be administered: 1.5 mL/dose
 
- Observational period: 4 weeks (up to 2 weeks after the 2nd dose)
 
- Number of visits: 5 visits
 
 
(1) Visit 1: screening and 1st dosing (Day 1)
 
(2) Follow up 1 (Telephonic visit – till 3 days after the 1st dose)
 
(3) Visit 2: 2nd dosing (14 + 3 days)
 
(4) Follow up 2 (Telephonic visit – till 3 days after the 2nd dose)
 
(5) Visit 3: 2 weeks after the 2nd dosing (28 + 3 days)
 
This will be carried out in healthy adults and children. Randomization will be stratified according to age <math>\geq 18</math> years to 60 years, <math>\geq 1</math> to <math><18</math> years.
 
According to the pre-generated randomization table, the subjects will be randomized to the test and comparator groups (Visit 1) and will be given either the test vaccine or the comparator vaccine. For immunogenicity assessment, the blood sample will be taken at Visit 1 (prior to investigational product dosing), Visit 2 (prior to investigational product dosing), and Visit 3 (after two weeks of the second dose).
 |

|                           |                                                                                                                                                                                                                                                                                                                                                                                                                                                                                                                                                                                                                                                                                                                                                                                                                                                                                                                                                                                                                                                                                                                                                                                                                                                                                                    |
|---------------------------|----------------------------------------------------------------------------------------------------------------------------------------------------------------------------------------------------------------------------------------------------------------------------------------------------------------------------------------------------------------------------------------------------------------------------------------------------------------------------------------------------------------------------------------------------------------------------------------------------------------------------------------------------------------------------------------------------------------------------------------------------------------------------------------------------------------------------------------------------------------------------------------------------------------------------------------------------------------------------------------------------------------------------------------------------------------------------------------------------------------------------------------------------------------------------------------------------------------------------------------------------------------------------------------------------|
|                           | At both follow up telephonic visits after vaccination, the appointed field officer will contact subjects via telephone for 3 consecutive days after the dosing of the vaccine. For safety assessment, the subjects and/or parents/legally acceptable representatives will be instructed to record on the subject diaries adverse events that occur after investigational product dosing.                                                                                                                                                                                                                                                                                                                                                                                                                                                                                                                                                                                                                                                                                                                                                                                                                                                                                                           |
| Inclusion Criteria | 
 
1. Individuals aged 1 year to 60 years both inclusive
 
2. Voluntary written informed consent form for study participation provided by an individual or his/her legally acceptable representative. Subjects aged 12 to <18 years, must sign an assent for the study and a parent or a legal guardian have to sign the informed consent. Subject aged 7 to 11 years need to provide an oral consent/assent and the consent form must be signed by parent/legally acceptable representative. Less than 7 years no need of assent, LAR can give consent
 
3. An individual who can be followed up during the study period and is capable of complying with the study requirements.
 
4. Healthy subjects as determined by: Medical history, Physical examination and Clinical judgment of the investigator
 
                                                                                                                                                                                                                                                                                                                                                                                                                  |
| Exclusion Criteria | 
Any one of the following
 
 
1. History of cholera vaccinations or history of cholera.
 
2. History of hypersensitivity reactions to other preventative vaccinations.
 
3. Immune function disorders including immunodeficiency diseases.
 
4. 38°C or higher body temperature measured prior to investigational product dosing.
 
5. Diarrhea or abdominal pain lasting 2 weeks or longer within 6 months prior to study initiation. Also, administration of antidiarrheal drugs or antibiotics to treat diarrhea within 1 week prior to study initiation.
 
6. Abdominal pain, nausea, vomiting, or decreased appetite within 24 hours prior to study initiation.
 
7. Pregnant or lactating women should be excluded by performing urine pregnancy test during screening.
 
8. Children vaccinated within 1 month prior to study initiation or planned vaccination during the study.
 
9. Participants in another clinical trial with investigational product dosing within 6 months prior to study initiation.
 
10. An individual thought to have difficulty in participating the study due to severe chronic diseases, based on the judgment of the investigator.
 
 |

|                             |                                                                                                                                                                                                                                                                                                                                                                                                                                                                                                                                                                                                                                                                                                                                                                                                                                                                                                                                                                                                                                                                                                                                                                                                                                                                                                                                                                                                                                                                                                                                                                                                                                                                                       |
|-----------------------------|---------------------------------------------------------------------------------------------------------------------------------------------------------------------------------------------------------------------------------------------------------------------------------------------------------------------------------------------------------------------------------------------------------------------------------------------------------------------------------------------------------------------------------------------------------------------------------------------------------------------------------------------------------------------------------------------------------------------------------------------------------------------------------------------------------------------------------------------------------------------------------------------------------------------------------------------------------------------------------------------------------------------------------------------------------------------------------------------------------------------------------------------------------------------------------------------------------------------------------------------------------------------------------------------------------------------------------------------------------------------------------------------------------------------------------------------------------------------------------------------------------------------------------------------------------------------------------------------------------------------------------------------------------------------------------------|
|                             | 
11. An individual thought to have difficulty in participating the study due to other reasons, based on the judgment of the investigator
 
12. If female patient will get pregnant after first vaccination.
                                                                                                                                                                                                                                                                                                                                                                                                                                                                                                                                                                                                                                                                                                                                                                                                                                                                                                                                                                                                                                                                                                                                                                                                                                                                                                                                                                                                                                                                |
| Endpoints            | 
Primary immunogenicity endpoint:
 
Assessment of seroconversion rate
 
 
The proportion of subjects with at least 4 times higher anti-V. cholerae O1 Ogawa and Inaba antibody titer at 2 weeks after the second dose (Visit 2) as compared to baseline titers prior to investigational product dosing (Visit 1).
 
 
Secondary immunogenicity endpoints:
 
 
The proportion of subjects with at least 4 times higher anti-V. Cholerae O139 antibody titer at 2 weeks after the second dose (Visit 2) as compared to baseline titers prior to investigational product dosing (Visit 1).
 
Geometric Mean Titer (GMT) and Geometric Mean Ratio (GMR) as measured by anti-V. Cholerae O1 Ogawa and Inaba antibody titer at 2 weeks after the second dose (Visit 2) as compared to baseline titers prior to investigational product dosing (Visit 1).
 
Geometric Mean Titer (GMT) and Geometric Mean Ratio (GMR) as measured by anti-V. Cholerae O139 antibody titer at 2 weeks after the second dose (Visit 2) as compared to baseline titers prior to investigational product dosing (Visit 1).
 
 
Safety endpoints:
 
From enrolment until end of the study period in:
 
 
Solicited adverse events (Day 0 ~ 3) post each vaccination dose and Unsolicited adverse events including abnormal vital signs and physical examination, throughout the study.
 
SAE including abnormal vital signs and physical examination, throughout the study.
 
 |
| Statistical Analysis | 
Data obtained from the study subjects will be analyzed in three forms; safety set, Intention to Treat (ITT) set, and Per Protocol (PP) set. Descriptive statistics will be used to define baseline characteristics, Mean and SD will be used to report AEs
 
Seroconversion rates will be compared using the chi-square test with Yates correction or the Fisher's exact test
 
Serum vibriocidal titers will be reported using Geometric mean titers (GMT) and Geometric mean fold rise (GMFR). A p-value of less than 0.05 will be considered the threshold to claim statistical significance.
                                                                                                                                                                                                                                                                                                                                                                                                                                                                                                                                                                                                                                                                                                                                                                                                                                                                                                                                                                                                                                                                     |

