To ensure the reformulated vaccine could be made available internationally, IVI facilitated a technology transfer between VaBiotech and Shantha Biotechnics Ltd., a private biotech company in Hyderabad, India (acquired by Sanofi in 2009), a country with a national regulatory authority certified as fully functional by WHO. In parallel with the technology transfer, IVI, in collaboration with India's National Institute of Cholera and Enteric Diseases (NICED), conducted a cluster-randomized, placebo-controlled efficacy trial with the reformulated vaccine in Kolkata, India. The two-dose vaccine was shown to provide a protective efficacy of 65% for at least 5 years and this was the first ever demonstration of strong sustained protection by an oral cholera vaccine. In 2009, the vaccine was licensed in both Vietnam (mORCVAXTM) and India (Shanchol), and in 2011, Shanchol was approved by the WHO Prequalification. Several clinical trials have been done on Shanchol vaccine in India in past as summarized below;

- **Immunogenicity study of OCV, Kolkata, India (NCT00419133):**

An open label randomized, placebo-controlled trial was conducted to assess the immune responses following one and two doses of the bivalent killed, whole-cell, oral cholera vaccine among adults and children in Kolkata, India. The study assessed whether receipt of a single dose of OCV is as immunogenic as receipt of two doses among adults and children residing in cholera-endemic areas in Kolkata. In addition, the safety of the OCV was also assessed after each dose. The rates of seroconversion after the second dose were found to be 46% of adults and 82% of children.

- **Study on dose-flexibility of OCV, Kolkata, India (NCT 01233362):**

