#### **Cohort 2 children:**

Test: 104 subjects

Reference: 104 subjects

Total Sample size with 10% Dropout is 416. As per published clinical study evaluating immunogenicity of Shanchol and Euvichol, the seroconversion rates (4-fold rise in antibody titres) 14 days after first and second dose of vaccine ranges from 73% to 90% in adults and children. Assuming seroconversion rate of 70% in the reference arm, power of 90%, alpha of 5% (2-sided) and a non-inferiority margin of 10%, 186 subjects would be required in the test and reference arms to establish non-inferiority of the vaccine.

Considering a dropout rate of 10%, a total of 416 subjects will be enrolled in the study (208 in Test and 208 in reference arms).

Approximately 208 subjects enrolled in the study will be adults ( $\geq 18$  to 60 years of age) while remaining 208 would be children ( $\geq 1$  to  $<18$  years of age).

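### The named seroconversion test ignores the age cohort used to stratify randomisation, and titres get no baseline-adjusted comparison between vaccines; the loss of precision is modest and free to recover.

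*Supplement*

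**What the plan says.** - **Randomisation.** Section 3.0, Study Methodology: "Randomization will be stratified according to age", with strata of 18 to 60 years and 1 to under 18 years. Sections 6.2 and 6.4 give two cohorts of 208, allocated 1:1, so 104 per arm in each.
- **Baseline titre.** Blood is drawn from every subject before the first dose (Sections 3.0, 8.1 and 8.2). The primary endpoint is a rise of at least four-fold over that value (Section 4.8).
- **Seroconversion comparison.** The Statistical Analysis row of Section 3.0 names a chi-square test with Yates correction, or Fisher's exact test, and a 0.05 significance threshold. Section 12.0 adds the analysis sets and repeats the threshold. Neither mentions a stratum, a cohort term or a covariate.
- **Titres.** Same row: "Serum vibriocidal titers will be reported using Geometric mean titers (GMT) and Geometric mean fold rise (GMFR"). The GMT and GMR endpoints in Section 4.8 are likewise set against the subject's own baseline. No Euvichol-Plus to Shanchol ratio is defined.
- **Age and response.** Section 4.0 cites a Kolkata immunogenicity study with seroconversion after the second dose of "46% of adults and 82% of children". In the Vellore post-licensure study the second-dose rates in adults and children were 45.8% and 67.7% for Ogawa, and 55.2% and 68.8% for Inaba.

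**The concern.** When randomisation is balanced within strata that differ in outcome, the difference between arms no longer carries the between-stratum variation. An analysis that pools the strata still counts that variation as error, so its standard error is too large. The protocol's background gives reason to expect different response rates in adults and children, yet the named test makes no use of cohort.

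For titres, the primary objective is comparison with Shanchol. Fold rise within an arm describes that arm; it is not a comparison of the two vaccines. Fold rise subtracts baseline on the log scale, which is not the same as adjusting for it and is in general less efficient.

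What is at stake is precision, in a trial where the expected half-width of the interval lies close to the 10-point margin.

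**Working it through.** **1. The plan's own figure.** Section 6.2 states that "186 subjects would be required in the test and reference arms to establish non-inferiority of the vaccine", from a 70% reference rate, 90% power, two-sided 5% alpha and a 10-point margin. The test-arm rate is not stated. The usual formula is

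n per arm = (1.960 + 1.2816)² × [pT(1−pT) + pC(1−pC)] / (0.10 + pT − pC)²

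- pT = pC = 0.70: 10.507 × 0.42 / 0.01 gives 442.
- pT = 0.75, pC = 0.70: 10.507 × 0.3975 / 0.0225 gives 186.

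So 186 is reproduced only with an unstated test rate of 75%. With both vaccines at 70%, 186 per arm gives 55.7% power. Dropout: 186 / 0.9 = 206.7, so 207; the plan has 208 per arm. The low power with equal vaccines is therefore present before any question of stratification.

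**2. Effect of stratifying by cohort.** Inputs: 186 evaluable per arm (93 per cohort), equal vaccines, a 10-point margin, and the cited cohort rates a (adults) and c (children).

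- Pooled variance term: vU = p(1−p), with p = (a+c)/2.
- Within-cohort term: vS = [a(1−a) + c(1−c)]/2.
- Half-width = 1.96 × √(2v/186). Power = Φ(0.10/√(2v/186) − 1.96).

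For Kolkata, vU = 0.64 × 0.36 = 0.2304 and vS = (0.2484 + 0.1476)/2 = 0.1980. The ratio vS/vU is 0.859 and √0.859 = 0.927.

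| Cited rates (adults / children) | vU | vS | Half-width, points | Narrower by | Power |
|---|---|---|---|---|---|
| Kolkata 46% / 82% | 0.2304 | 0.1980 | 9.76 to 9.04 | 7.3% | 52.0% to 58.2% |
| Vellore Ogawa 45.8% / 67.7% | 0.2454 | 0.2335 | 10.07 to 9.82 | 2.5% | 49.5% to 51.4% |
| Vellore Inaba 55.2% / 68.8% | 0.2356 | 0.2310 | 9.87 to 9.77 | 1.0% | 51.1% to 51.9% |

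If the 73% to 90% planning range of Section 6.2 is taken as the two cohort rates (an assumption), the interval narrows by 2.4% and power moves from 70.0% to 72.1%.

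**3. Simulation check.** With 200,000 trials per row and cohort-stratified allocation, the true SD of the difference and the mean unstratified standard error were:

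- Kolkata: 0.0463 against 0.0497; the unstratified 95% interval covered 96.3%.
- Vellore Ogawa: 0.0503 against 0.0512; coverage 95.2%.
- Vellore Inaba: 0.0497 against 0.0502; coverage 95.2%.

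The unstratified analysis errs on the cautious side. A simple stratified Wald interval covered 94.7% to 94.8%, which favours a score-type interval.

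**4. What stratifying does not do.** With stratification, 90% power for equal vaccines would still need 417 (Kolkata), 486 (Vellore Inaba) or 491 (Vellore Ogawa) per arm.

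**5. Titres.** Adjusting the final log titre for baseline multiplies its residual variance by 1 − r², where r is the correlation between baseline and final log titre. The documents give no r. For an assumed r of 0.3 to 0.6 the factor is 0.91 to 0.64. Compared with fold rise, and assuming equal variance at both visits, the factor is (1+r)/2, or 0.65 to 0.80. These figures are illustrative only.

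**The case against.** **Baseline is already used.** A reader might infer that the planned comparisons disregard baseline titre. They do not: it defines the four-fold rise, the GMR and the fold rise. Only covariate adjustment is missing.

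**No interval is planned.** One might conclude that the trial's intervals will be too wide. The protocol specifies no between-arm interval at all, and its named tests are tests of equality. The half-widths above describe the interval that would match an unstratified analysis. The missing interval against the margin is a separate and larger gap.

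**Pooling is not stated.** The Statistical Analysis row does not say whether the test is run once on all subjects or within each cohort. The 186 per arm implies pooling. If cohorts were tested separately, the variance argument would fall away, but each would have about 93 evaluable per arm and, at 70% in both arms, 31.8% power.

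**The age contrast is not uniform.** Section 4.0 also cites a Kolkata non-inferiority trial that found no significant difference in response between ages 6–14 and over 15. Those are not this trial's strata, but the Kolkata 46%/82% contrast is the most favourable case for stratifying and should not stand alone.

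**This is SAP material.** No SAP is shown, and weights and covariates are often left to one. That stands as to detail. The point survives because the protocol itself names a test, and that test leaves out the stratification factor.

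**Validity is not threatened.** This stands. Ignoring the stratum does not inflate type I error.

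**Conclusion.** The point holds as a modest loss of efficiency. The stated seroconversion test does not account for the stratification factor, and the titre analysis provides no baseline-adjusted comparison of the two vaccines. On the cited cohort rates, stratifying narrows the 95% interval by about 1% to 7% and adds about 1 to 6 points of power. This assumes equal vaccines, 186 evaluable per arm split evenly between cohorts, a pooled analysis, and cohort rates like those in the Kolkata and Vellore studies. The gain from baseline adjustment has no documented size.

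Two stronger readings are not supported. The unstratified test is conservative, so it does not make a non-inferiority claim invalid. Nor is it the cause of the 50% to 56% power with equal vaccines: that comes from the sample-size calculation, and stratifying does not repair it.

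**What to change.** In the Statistical Analysis row of Section 3.0 and in Section 12.0, state the following:

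1. **Seroconversion.** The primary comparison is the risk difference, Euvichol-Plus minus Shanchol, stratified by the two age cohorts with Mantel-Haenszel weights and a stratified Miettinen-Nurminen 95% interval, judged against the 10% margin. Each cohort's difference and interval are supportive, given the roughly 32% power for a separate claim.
2. **Titres.** Log titre at 2 weeks after the second dose is analysed by ANCOVA on arm, log baseline titre and cohort. The Euvichol-Plus/Shanchol GMT ratio is reported with its 95% interval for Ogawa, Inaba and O139. Fold rise within arm stays as description.

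The cost is wording and some programming. No new data, visits or subjects are needed. With 1:1 allocation in equal cohorts, the Mantel-Haenszel weights are one half each, so the stratified estimate is close to the crude difference and the main change is to the standard error.
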